## Abstract

**Background:**

Nonadherence to treatment leads to suboptimal treatment outcomes and enormous costs to the economy. This is especially important in Parkinson’s disease (PD). The progressive nature of the degenerative process, the complex treatment regimens and the high rates of comorbid conditions make treatment adherence in PD a challenge. Clinicians have limited face-to-face consultation time with PD patients, making it difficult to comprehensively address non-adherence. The rapid growth of digital technologies provides an opportunity to improve adherence and the quality of decision-making during consultation. The aim of this randomised controlled trial (RCT) is to evaluate the impact of using a smartphone and web applications to promote patient self-management as a tool to increase treatment adherence and working with the data collected to enhance the quality of clinical consultation.

**Methods/Design:**

A 4-month multicentre RCT with 222 patients will be conducted to compare use of a smartphone- and internet-enabled Parkinson’s tracker smartphone app with treatment as usual for patients with PD and/or their carers. The study investigators will compare the two groups immediately after intervention. Seven centres across England (6) and Scotland (1) will be involved. The primary objective of this trial is to assess whether patients with PD who use the app show improved medication adherence compared to those receiving treatment as usual alone. The secondary objectives are to investigate whether patients who receive the app and those who receive treatment as usual differ in terms of quality of life, quality of clinical consultation, overall disease state and activities of daily living. We also aim to investigate the experience of those receiving the intervention by conducting qualitative interviews with a sample of participants and clinicians, which will be administered by independent researchers.

**Trial registration:**

ISRCTN45824264 (registered 5 November 2013)

**Electronic supplementary material:**

The online version of this article (doi:10.1186/1745-6215-15-374) contains supplementary material, which is available to authorized users.

## Background

### Parkinson’s disease

Parkinson’s disease (PD) is a degenerative movement disorder affecting 1% to 2% of the population over 60 years of age [1]. In one study on incidence rates, researchers reported that 0.5% of patients were diagnosed before the age of 40 years, 3.5% before the age of 50 years and more than 60% between the ages of 65 and 79 years [2]. The core motor features of PD comprise combinations of bradykinesia, resting tremor, rigidity, flexed posture, ‘freezing’ and loss of postural reflexes [3]. PD is a disabling condition with significant impact on quality of life (QoL) [4]. Notably, nonmotor symptoms of PD, such as dementia, sleep disturbances, depression and falls, may also have a significant negative impact on QoL [5]. Comorbidity is common in PD. Longitudinal studies have shown that people with PD have a three to six times higher risk of developing dementia than do people of the same age who do not have PD [6, 7]. PD is associated with significant burden of illness and cost to society. Increases in physician and drug costs and longer hospital admissions compared to age- and sex-matched controls have also been reported [8].

### Complexity of treatment

Managing both motor and non-motor symptoms of PD translates into complex treatment regimes. Treatment regimens are planned based on the stage of the illness- early or late- and on the type and mix of nonmotor symptoms [9]. The risk of side effects from treatment adds to the complexity of managing PD (Table 1). In early stages of the disease, patients usually take a single drug [9, 10] but in later stages of the disease more than half of the patients with PD take two to three drugs three to four times daily [11, 12].

**Table 1 Tab1:** **Current available pharmacological treatment and side effects for early and late Parkinson’s disease**
^**a,b**^

Therapy	Risk of side effects	
	***Motor complications***	***Other side effects***
Adjuvant therapy for early PD		
Levodopa	↑**	↑***
Dopamine agonists	↓	↑
MAO-B inhibitors	↓	↑
β-adrenergic antagonists	Lack of evidence	
Amantadine	Lack of evidence	
Anticholinergics	Lack of evidence	
Modified-release levodopa	↑	↑
**Adjuvant therapy for late PD**		
Dopamine agonists	↓	↑
MAO-B inhibitors	↓	↑
COMT inhibitors	↓	↑
Amantadine	↓	↑
Apomorphine	↓	↑
Modified-release levodopa	↓	↑

^a^
*Adapted from* National Institute for Health and Care Excellence (NICE) [9]*.*
^b^COMT, Catechol-O-methyltransferase; MAO*-B, Monoamine oxidase B; PD, Parkinson’s disease. ↑** Evidence of increased motor complications/other adverse events. ↓*** Evidence of reduced motor complications/other adverse events.*

### Treatment nonadherence

Adherence to long-term therapies in the general population is around 50% in the developed world [13]. Nonadherence results in failed treatment outcomes and $100 billion spent each year worldwide on avoidable hospitalizations [14]. There are various predictors of medication nonadherence, including the following ones set forth by Osterberg and Blaschke [15]:

Presence of psychological problems, particularly depressionPresence of cognitive impairmentTreatment of asymptomatic diseaseInadequate follow-up or discharge planningSide effects of medicationPatient’s lack of belief in the benefit of treatmentPatient’s lack of insight into the illnessPoor provider–patient relationshipPresence of barriers to careMissed appointmentsComplexity of treatmentCost of medication, copayment or both

Adherence is inversely proportional to the frequency of dose, with patients taking medication on a schedule of four times daily achieving average adherence rates of about 50% [16]. Some clinicians propose that medication nonadherence should be conceptualised as a diagnosable and treatable medical condition [17]. The ability of physicians to recognize nonadherence is poor, and interventions aimed at improving adherence have had mixed results and are costly [15, 18].

Adherence to medication regimens is an essential prerequisite for symptom control in PD [19]. Rates of adherence to treatment in PD mimic those of other long-term conditions, with one research group reporting that 51.3% of subjects missed at least one dose per week and 20.5% of subjects missed three or more doses per week [20]. The authors of a systematic review of factors associated with nonadherence in PD patients reported six clinical factors (mood disorders, cognitive impairment, poor symptom control or reduced QoL, younger age or longer disease duration, and regime complexity or polypharmacy) and five demographic factors (lack of spouse or partner, low income, employment status, and gender) associated with nonadherence [19].

There are direct and indirect methods of measuring adherence. Direct methods include directly observed therapy, measurement of level of medicine or metabolite of medicine in blood, and measurement of biological markers in blood [17, 21]. Indirect methods include patient questionnaires, patient self-reports, pill counts, rates of prescription refills, assessment of patient’s clinical response, electronic medication monitors and patient diaries [17, 21]. Though certain methods are preferred in specific clinical or research settings, a combination of measures maximizes accuracy [22].

### Shared decision-making

Patients are increasingly taking active roles in decisions about major medical interventions, such as hip replacement surgery, and about routine decisions, such as medication initiation [23]. However, there is evidence on shared decision-making between patient and clinician that, though patients are well-advised to learn about the potential benefits and risks of relevant alternatives before a treatment decision is reached [24], this is not followed in most clinical settings due to clinician and patient factors [23, 25, 26]. In a large-scale survey of PD patients in Sweden, researchers found that doctors provided only a small proportion of patients with advanced therapy information, despite patients’ interest [27].

### Digital health care

The use of digital technology in daily life has become ubiquitous. As of 2012, 76% of the UK population had access to broadband connections and 92% of adults personally owned or used mobile phones, of which 60% were smartphones (that is, mobile phones with features of a handheld computer, such as internet access, data storage, email capability and voice and video recording) [28, 29]. The authors of a recent systematic review on the use of mobile phones in health care reported that voice and text messaging services are used to improve health outcomes (medication compliance, asthma symptoms, haemoglobin A1C control, stress levels, smoking quit rates, and self-efficacy) and processes of care (fewer missed appointments, quicker diagnosis and treatment, and improved teaching and training) [30]. Evidence on the use of smartphones to improve clinical outcomes is also gathering momentum [31]. The push to use digital technologies in the UK National Health Service (NHS) to improve clinical outcomes has increased in recent years, with the Whole Systems Demonstrator study investigators reporting that telehealth services substantially reduce mortality, the need for hospital admissions, the number of bed days spent in hospital and the time spent in the accident and emergency department [32].

Smartphones have been used in managing PD to assess pervasive movement analysis remotely [33] and for predicting the risk of falls [34]. The SMART-PD trial was preceded by a 2 –month pilot trial carried out by uMotif Ltd, Birkbeck University of London and The Cure Parkinson’s Trust. Here researchers evaluated the impact of a patient-led tracker mobile application (an ‘app’) to improve medication regime adherence among PD patients from December 2012 to March 2013 [[name], [name], [name], [name] Self-management in long-term conditions using smartphones: A pilot randomised trial in Parkinson’s disease (submitted)]. A total of 36 patients with PD took part in a 55-day pilot study and were randomised into two groups. The limited-app group (*n* = 19) received an app which had tools for daily self-tracking on ten measures of symptom severity, general well-being and health behaviours, along with a daily diary. The full-app group (*n* = 17) received an app which had the same tools as the limited-app group with the addition of medication reminders and two games to assess cognition. Participants used the app for 55 days and entered data on at least 70% of those days.

### Study rationale

Despite evidence highlighting nonadherence to medication regimes among patients with PD and a lack of evidence on shared decision-making, there is little evidence on interventions that improve adherence to PD treatment. Following up on the findings of the 2-month pilot trial study on patient-led use of a tracker app [35], in this follow-up study we aim to evaluate the impact of using a Parkinson’s tracker app (PTA) along with treatment as usual (TAU) on medication adherence in a larger number of patients across multiple trial sites.

We hypothesise that encouraging patients to track their symptoms and medication intake regularly may result in increased medication adherence. Furthermore, we postulate that using data collected by the patient may lead to better symptom control, an improved QoL and a higher quality of clinical consultation.

### Trial objectives

#### Primary objectives

Our primary objective is to investigate whether patients with PD who use the PTA in addition to TAU show improved medication adherence.

#### Secondary objectives

A secondary objective is to investigate whether patients who receive the PTA and those who receive TAU differ in terms of QoL, quality of clinical consultation, overall disease state, activities of daily living (ADL), beliefs about medication and generic health-related QoL. We also aim to investigate the experiences of those receiving the intervention by gathering information from qualitative interviews administered by independent researchers.

## Methods/Design

A single-blind, multicentre RCT will be conducted to compare use of smartphone- and internet-enabled PTA with TAU among patients with PD and/or their carers across seven centres in England and Scotland. The trial has received ethical approval from the National Research Ethics Service London–Westminster Research Ethics Committee (13/LO/1783).

### Trial participants

Patients diagnosed with PD attending neurology outpatient (OP) appointments or research clinic appointments at participating sites will be enrolled into the trial over a 16-week period. We have adapted the inclusion and exclusion criteria from a similar study on treatment adherence in PD patients [35].

To be eligible for the trial, patients must meet the following criteria: (1) older than 21 years of age; (2) diagnosed with probable, idiopathic PD; (3) prescribed one or more antiparkinsonian medications; (4) English-speaking and literate (that is, can read, write and speak in English and compute and solve problems at levels of proficiency necessary to function daily at a job and/or in ADL); (5) have access to a smartphone and/or tablet or internet on a daily basis at home; (6) be on a stable medication regime (that is, not altered within the previous month and not expected to change during the period of the trial (16 weeks), with alteration of doses of existing medications considered to be a stable medication regime); and (7) without a diagnosis of dementia or significant cognitive impairment (as recorded in patient case file). The clinical team will judge whether the patient has the cognitive capacity required to participate fully in the trial (that is, read patient information, complete self-report questionnaires and sign informed consent form).

The following are the exclusion criteria: (1) suspected parkinsonism due to causes other than idiopathic PD, (2) current or previous treatment with antiparkinsonian medications (anticholinergics) for side effects of prolonged neuroleptic treatment, (3) diagnosis of dementia or significant cognitive impairment (as recorded in patient case file), (4) current or previous diagnosis of mental illness associated with psychosis (schizophrenia, severe depression with psychosis, bipolar affective disorder) (as recorded in patient file), and (5) detrimental illness with a short life expectancy.

Informed consent will be obtained from every trial participant.

### Outcome measures

The primary outcome measure is adherence to treatment as determined by Morisky Medication Adherence Scale (MMAS-8) score at 16 weeks [36, 37]. The response categories are ‘yes’ or ‘no’ for each item with a dichotomous response and a 5-point Likert response for the last item. A ‘yes’ response is scored as 1 and a ‘no’ has no score. The primary endpoint will be the total MMAS-8 score at 16 weeks. We are collecting data from a range of secondary outcome measures, including the following:

Parkinson’s Disease Questionnaire (PDQ-39) to measure QoL [38]Quality of consultation for PD patients (from the *Patient-Centered Questionnaire for PD*[39]Non-Motor Symptoms Scale [40]Hospital Anxiety and Depression Scale [41]Beliefs about Medication Questionnaire [42]

In addition to the measures listed above, we will collect demographic data at baseline, such as participant age, duration and severity of PD (Unified Parkinson’s Disease Rating Scale score if recorded in clinical file), medication profile (types of medication, dosage level and frequency), socioeconomic status, ethnicity, comorbidities, level of education and whether medication is self-administered or given by a spouse or carer. We also will collect patients’ self-reported ratings and game scores within the application.

### Randomisation and masking

Eligible patients for whom consent or assent is provided will be allocated in a 1:1 ratio to the two arms of the study according to a computer-generated random sequence stratified by centre and using blocks of variable size. The allocation sequence will be generated by the trial statistician and will not be available to any member of the research team until databases have been completed and locked. In view of the established safety record of study interventions, there will be no provision for emergency unblinding of participants, and copies of the allocation sequence will not be held at the recruiting centres.

### Recruitment procedures

Patients who are potentially eligible based on inclusion criteria (except inclusion criterion 4) will be identified by the clinical team across the seven trial sites from the clinic’s list 6 weeks prior to upcoming outpatient appointments. An information pack containing a patient invitation letter, a Participant Information Sheet and a consent form will be sent to potential participants 3 to 4 weeks prior to the next OP clinic appointment or separately with an OP clinical appointment date by post and/or by email, along with a request to reply within 1 week. Reminders will be sent by post and/or email sent 1 to 2 weeks before an OP appointment to those who fail to respond to email. At the OP appointment, the clinician will (1) recheck whether the participant has daily access to a smartphone or tablet or an internet connection and (2) assess whether a change in medication regime is needed. If the patient does not have such a connection and/or needs a change in medication regime, he or she will not be enrolled into the trial. However, these participants will be given free access to the app once the trial is completed. Patients sign a hard copy of the consent and complete the questionnaires at the clinic if it is possible to give them internet access at the clinic or if they can complete the questionnaires at home within 1 week after the OP appointment. If participants withdraw from the trial after giving consent, they will continue to receive the treatment they were receiving prior to the start of the trial (that is, TAU). Data collected up to the point of withdrawal will be retained for final analysis. Following consent, patients are randomised to either the intervention or the control group. Randomisation is carried out with sealed randomisation envelope for each participant generated by the trial statistician. The clinician runs through the details of the allocation—intervention or control—with the patient and gives him or her the date for follow-up. Recruitment will be a rolling programme over the course of 16 weeks until recruitment targets are achieved. Participants in the intervention group will get a call from their clinicians 2 weeks postrandomisation to check if they have any difficulties with the PTA. All participants get a call from their clinician 1 to 2 weeks prior to the follow-up appointment to remind them of their appointment. Participants complete the questionnaires within 1 week after their appointment.

The trial is being carried out in adherence to the Consolidated Standards of Reporting Trials (CONSORT) Statement [43] (Figure 1), and the protocol adheres to the guidelines for clinical trial protocols set forth in the SPIRIT 2013 Statement (Standard Protocol Items: Recommendations for Interventional Trials) Additional file 1: Table S1, [44].

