### Intervention group

#### Parkinson’s tracker app

Participants allocated to receive the intervention will receive instructions to download the PTA to their Android or iPhone smartphones or tablet devices or to access it via a website portal within 1 day after they have attended their outpatient appointment. The app consists primarily of the following features:

•Using a sliding petal interface (Figure 2), participants will adjust their daily scores on eight to ten self-monitoring measures on a 5-point scale: water, sleep, exercise, 5 A DAY healthy diet, mood and energy, medication, movement, suppleness and control. Participants who have difficulty manipulating the flower icon due to their motor symptoms will have the option of using an accessibility mode with a zoom function to magnify the screen. Participants will be able to review their scores and compare ‘petals’ against each other.

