## Discussion

There is a paucity of evidence on interventions to enhance treatment adherence in PD. Unlike previous studies in which researchers investigated adherence to therapy programmes, SMART-PD uses resources that patients and their carers and/or partners have (i.e. a smartphone or tablet device). By ensuring that the intervention is introduced in routine clinical practice with minimal need for additional resources, our aim in the SMART-PD trial is to demonstrate that adherence to treatment and quality of clinical consultation can be improved in a cost-effective manner. The subjective nature of the self-report instruments used in the trial is acknowledged. Patients may over- or underreport their true health status, depending on the trial arm to which they are assigned. To reduce this bias, baseline primary outcome measures will be completed within a maximum of 2 weeks of randomisation. The nature of the SMART-PD intervention does not allow masking of study participants blinded to their group allocation. Therefore, secondary outcomes at baseline (completed postrandomisation) and all follow-up study outcomes will not be blinded. The SMART-PD intervention is aimed at PD patients who have smartphones and/or tablet devices or internet access, thereby omitting those who do not have such access. To reduce this selection bias, we are including those patients whose carers and/or partners have a smartphone. However, with rapid penetration of smartphones in the UK, we expect this limitation to decrease rapidly. If effective, the trial results will demonstrate improved outcomes with the use of innovative smartphone technology for patients with long-term conditions and the clinicians who treat them.

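### Baseline questionnaires may be completed after the patient knows the allocation, yet the models adjust for them as baseline covariates, which can bias the treatment effect

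*Protocol article*

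**What the plan says.** All references are to the protocol article.

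- **Recruitment procedures, questionnaires.** Patients complete the questionnaires at the clinic if internet access can be given there, or they may "complete the questionnaires at home within 1 week after the OP appointment".
- **Recruitment procedures, randomisation.** "Following consent, patients are randomised to either the intervention or the control group". Consent is the only stated condition; a completed baseline form is not required.
- **Recruitment procedures, disclosure.** "The clinician runs through the details of the allocation—intervention or control—with the patient and gives him or her the date for follow-up".
- **Parkinson's tracker app.** Intervention patients are instructed to download the app or "access it via a website portal within 1 day after they have attended their outpatient appointment".
- **Discussion, primary baseline.** "baseline primary outcome measures will be completed within a maximum of 2 weeks of randomisation". The wording does not say whether this means before or after randomisation.
- **Discussion, secondary baselines.** "secondary outcomes at baseline (completed postrandomisation) and all follow-up study outcomes will not be blinded".
- **Discussion, reporting bias.** "Patients may over- or underreport their true health status, depending on the trial arm to which they are assigned". The two-week limit on the primary baseline is offered as the way to reduce this bias.
- **Statistical analysis.** The primary GLM has treatment as the fixed effect and baseline MMAS-8 as the covariate. Secondary outcomes are analysed in the same framework.

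**The concern.** Adjusting for a baseline is safe because, under randomisation, the arms differ on it only by chance. That protection goes once allocation, or use of the app, can influence the value. If early app use or awareness of the arm has already moved the recorded baseline, the model subtracts part of that movement from the 16-week comparison. A shift towards better adherence in the app arm dilutes the effect; a shift the other way inflates it.

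The protocol names a mechanism itself: reporting may depend on the assigned arm. A form completed soon after allocation does not keep that reporting out of the covariate. The order in which data are collected has to be fixed in the protocol, because an analysis plan cannot restore a baseline that was never taken before allocation.

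**Working it through.** **1. Order of events for a home completer in the app arm.** Day 0: appointment, consent, randomisation, disclosure of the arm. By day 1: app instructions or access. Up to day 7: baseline questionnaire. The baseline can therefore be recorded up to 7 − 1 = 6 days into app use. This takes randomisation to be at the appointment. The app timing supports that, because intervention patients could not be instructed within a day of the appointment unless they were already allocated.

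**2. The plan's own figure.** Inputs from Sample size: difference 1, SD 2.5, 80% power, 5% level (taken as two-sided).

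n per arm = 2 × (1.96 + 0.84)² × 2.5² / 1² ≈ 98.1, rounded up to 99, so 198 in total against the stated 200. With 100 per arm the unadjusted power is 80.7%. The stated sample size reproduces and is not in question.

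**3. Bias formula.** With equal SDs at both visits, the slope of the 16-week score on baseline equals the correlation r. If allocation moves the recorded app-arm baseline by s points in the direction of improvement:

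- expected estimate = true effect − r × s
- standard error = 2.5 × √(1 − r²) × √(2/100)

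The documents give neither r nor s, so both are assumptions. s is the mean over all patients in the arm. For example, a 0.5-point shift among home completers who make up half the arm gives s = 0.5 × 0.5 = 0.25; if everyone completes at home, s = 0.5.

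**4. Numbers, true effect 1 point, 100 per arm.** For r = 0.5 the standard error is 2.5 × √0.75 × √0.02 = 0.306.

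| r | s = 0 | s = 0.25 | s = 0.5 |
|---|---|---|---|
| 0.3 | 1.00 (84%) | 0.93 (78%) | 0.85 (71%) |
| 0.5 | 1.00 (90%) | 0.88 (82%) | 0.75 (69%) |
| 0.7 | 1.00 (98%) | 0.83 (90%) | 0.65 (73%) |

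Each cell is the expected estimate with power in brackets. For r = 0.5 and s = 0.5: 1 − 0.5 × 0.5 = 0.75; 0.75 / 0.306 = 2.45; 2.45 − 1.96 = 0.49, so power is about 69%. A shift in the opposite direction raises the estimate by the same amount. If s = 0 or r = 0 there is no bias.

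**5. What dropping the covariate does.** Suppose arm-dependent reporting of size d is present at baseline and persists unchanged to 16 weeks. The adjusted analysis then carries a bias of d − r × d = d(1 − r), and the unadjusted difference carries d. With d = 0.5 and r = 0.5 these are 0.25 and 0.5. The unadjusted analysis is therefore not automatically the safer one.

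**The case against.** **MMAS-8 may have been meant to come first.** The Discussion marks only the secondary baselines as completed after randomisation and leaves the primary baseline out of its list of unblinded measures. The CONSORT flowchart, which might show the order, is not available here. This stands as far as intent goes. A reader might infer that every MMAS-8 baseline is taken after allocation; the text does not support that, and clinic completers may well answer beforehand. But nothing in Recruitment procedures secures that order for home completers, and for secondary outcomes the order is stated.

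**The two windows.** A reader might infer that one week after the appointment and two weeks around randomisation contradict each other. They do not: if randomisation is at the appointment, a form returned within a week satisfies both. The trouble is that neither window is required to end before allocation.

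**The magnitude is assumed.** Correct. No document figure supports any particular shift or correlation, and a shift of 0.5 means that half the target effect, or an equivalent reporting change, is present within days on average across the arm. With s = 0.25 and r = 0.5, power is still 82%, above the planned 80%, although the estimate is biased.

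**False positives.** A reader might infer a markedly inflated type I error. That needs app patients to report worse adherence at baseline and the difference to vanish by 16 weeks, and it is largest if every baseline is post-allocation. The documents support none of these. In the more natural case of early benefit, the bias is towards no effect.

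**Intention to treat.** A reader might also infer that patients who never return the form fall out of the model and break intention to treat. Handling of a missing covariate is ordinary analysis-plan content, so this is no fault of the article.

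**Disclosure.** The Discussion is open about the secondary baselines and about arm-dependent reporting. That is fair credit, but disclosure does not protect the covariate.

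**Conclusion.** The concern holds as a risk that the protocol permits, not as a demonstrated bias. Post-allocation baselines are stated for the secondary outcomes and not prevented for MMAS-8 among home completers, and the planned models use baseline as the covariate. The resulting bias is about −(baseline slope) × (arm difference already present at baseline). Its size and direction are unknown and it scales with the share of patients who complete at home.

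The illustrative range, an expected estimate of 0.88 to 0.75 instead of 1 and power of 82% to 69% instead of 90%, rests on SD 2.5, 100 per arm, r = 0.5 and a mean shift of 0.25 to 0.5 point towards improvement. The first two come from the protocol; the last two are assumptions. The sample size is unaffected.

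**What to change.** **Protocol text.** Amend Recruitment procedures and the Discussion so that MMAS-8, and preferably every baseline questionnaire, must be submitted before the randomisation envelope is opened. Home completers are randomised once their online form has been received. Replace the two-week allowance with a window that ends before randomisation. The sentence tying app instructions to the appointment needs to be reconciled with this order.

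**Patients already enrolled.** Trial status gives a recruitment start of 12 August 2014, so some may be. Record each baseline completion date relative to randomisation. Pre-specify a sensitivity analysis that omits post-allocation baselines as covariates, and state that the unadjusted difference is still exposed to unblinded reporting at follow-up.

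**Cost.** No extra patients or visits. Home completers learn their allocation and get app access a few days later, by phone or online, so for them disclosure moves out of the clinic. That is a modest change to site procedure.
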